### Non-communicable diseases are a leading cause of death in MDA

While NCDs are a global epidemic, MDA ranks among the countries most affected. Nearly 90% of all deaths in MDA are caused by NCDs, the majority of which (55%) are caused by CVD.^7^ In 2016, the probability of dying prematurely from any of the four major NCDs (CVDs, cancer, diabetes, chronic respiratory disease) was 24.9%; almost twice as high for men (33.7%) as women (17.3%).^8^ Men and people residing in rural areas are disproportionally impacted by CVD and represent key populations for public health intervention.^7^

This burden is driven by some of the highest rates of NCD risk factors, including tobacco and alcohol use, in the WHO European region indicated by a 2013 Stepwise Appraoch to Surveillance (STEPS) survey.^9^ One in four (25.3%) Moldovans smoke tobacco and this rate nearly doubles in men.^9^ Among adults aged 18–69 years, 61.9% currently consume alcohol and one in five people have engaged in heavy episodic drinking (six or more drinks on any one occasion in the past 30 days).^9^

The overall prevalence of obesity among adults is 22.9%, being higher among women (28.5%) as compared with men (17.8%).^9^ The prevalence of raised blood pressure (defined as systolic blood pressure ≥140 mm Hg and/or diastolic blood pressure ≥90 mm Hg or currently taking medication for raised blood pressure) among MDA’s adult population is 39.8%, and 76.2% of these patients are not on blood pressure-lowering medication.^9^ A total of 12.3% of the population have a blood glucose level of ≥6.1 mmol/L, and 29.4% of the population has a total blood cholesterol level of ≥5 mmol/L.^9^ It is estimated that one in five (23.0%) people aged 40–69 years have a 10-year fatal or non-fatal CVD risk of over 30% (including those with an existing CVD).^9^

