### Essential interventions to prevent cardiovascular diseases in primary healthcare

In order to build capacity in primary healthcare and ultimately prevent premature mortality from CVD in MDA, a study was envisioned to adapt and pilot the WHO Package of Essential NCD Intervention from Primary Healthcare in Low Resource Settings (WHO PEN).^3^ WHO PEN includes simplified clinical protocols which together cover the integrated management of hypertension and diabetes, as well as education and counselling on healthy behaviours aimed to prevent CVD. The central strategy of this integrated approach is the use of total cardiovascular risk assessment to stratify and target individuals at high CVD risk, a process considered to be a ‘best buy’ intervention by WHO.^5^

These interventions are aimed at tackling areas identified in a 2014 WHO assessment of challenges and opportunities for better NCD outcomes in MDA.^13^ This includes shortcomings among health workers in the identification and management of individuals with increased cardiovascular risk. The interventions are expected to add to the current quality of care by targeting interventions (non-pharmacological and/or pharmacological) to those at highest risk who stand to gain the most in absolute cardiovascular risk reduction, while also emphasising improvements in the organisation of care. The intervention also includes practical face-to-face training and follow-up implementation support. Current practice underuses these medical strategies and guidelines (eg, CVD risk score directed primary prevention), in addition to limited task sharing with non-physician health workers (eg, nurses) in these care pathways.^13^ At the study’s inception, there were no known developments beyond the scope of this project that could change clinical practice for NCDs in primary healthcare.

Since the use of WHO PEN was unprecedented in MDA, the Ministry of Health, Labour and Social Protection convened a national steering group to lead the adaptation and pilot process, with the goal of using the findings for future health systems development. Led by the primary healthcare division of the Ministry of Health, the steering group comprises representatives from the Nicolae Testemitanu State University of Medicine and Pharmacy and the National Public Health Agency. The national steering group is supported by an international team of experts coordinated jointly by the WHO Regional Office for Europe and WHO Country Office in MDA.

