Are statins prescribed correctly based on documented risk score?	Proportion of patients eligible based on documented risk score prescribed a statin.	Patients with a documented risk score as very high risk SCORE≥15% prescribed a statin.	Patients with a documented risk score as very high risk SCORE≥15%.
Are patients with existing disease, who do not require the calculation of a risk score to prescribe satins, prescribed statins?	Proportion of patients with existing CVD prescribed a statin.	Patients with existing CVD prescribed a statin.	Patients with existing CVD.
Is the blood pressure of high-risk patients controlled?	Proportion of high-risk patients (SCORE≥15% or DM and age over 40 years) whose last two recorded blood pressure measurements were <130/80 mm Hg.	Patients with a true risk score indicating a very high risk (SCORE≥15%) or DM and age over 40 years whose last two documented blood pressure readings were <130/80 mm Hg.	Patients with a true risk score indicating a very high risk (SCORE≥15%) or DM and age over 40 years.
Is the blood pressure of low-risk patients controlled?	Proportion of low-risk patients (SCORE<15%) whose last two recorded blood pressure measurements were <140/90 mm Hg.	Patients with a true risk score indicating <15% whose last two documented blood pressure readings were <140/90 mm Hg.	Patients with a true risk score indicating <15%.
Are patients with existing CVD prescribed basic medications to reduce risk?	Proportion of patients with existing CVD prescribed a statin and aspirin and blood pressure-lowering treatment.	Patients with existing CVD prescribed a statin and aspirin and blood pressure-lowering treatment.	Patients with existing CVD.
Is the blood glucose of patients with diabetes controlled?	Proportion of patients with diabetes with glycaemic control as defined by last two HbA1c measurements.	Patients with type 2 diabetes whose last two HbA1c measurements were below personal target as defined by MDA-adapted WHO PEN protocol 1.	Patients with type 2 diabetes.
Is the blood pressure of patients with hypertension controlled?	Proportion of patients with confirmed hypertension whose systolic blood pressure is <140/90 mm Hg at last two visits.	Patients with confirmed hypertension whose last two blood pressure readings were <140/90 mm Hg.	Patients with confirmed hypertension.

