### Data collection and management

#### Quantitative data collection tool

A standardised data collection template has been developed for extracting anonymised patient data from individual paper records (table 2). An online version was also made to allow for data entry on a computer or smartphone. It is estimated to take 15 min to extract data from one patient record since the records are made of blank paper with no formal structure or organisation of health data.

**Table 2 T2:** Standardised data collection form used to extract data from individual patient records

Data collection question	Answer
What is your name? (Name of person extracting data)	
Date of data extraction (MM-DD-YYYY)	
Write the clinic name	
Is this a duplicate extraction?	
If it is a duplicate extraction, enter the number you and your extraction partner have assigned to this file.	
Date of birth (MM-DD-YYYY)	
Sex (M/F)	
Smoking status (Y/M)	
Diagnosis of hypertension (Y/N)	
Date of hypertension diagnosis (MM-DD-YYYY)	
Can you find one or more blood pressure readings? (Y/N)	
Most recent systolic blood pressure	
Most recent diastolic blood pressure	
Date of the most recent blood pressure measurement (MM-DD-YYYY)	
Can you find a second most recent blood pressure reading? (Y/N)	
Second most recent systolic blood pressure	
Second most recent diastolic blood pressure	
Date of the second most recent systolic blood pressure (MM-DD-YYYY)	
Diagnosis of diabetes (type 1, type 2, no)	
Can you find one or more glycated haemoglobin (HbA1c) measurements? (Y/N)	
Most recent HbA1c reading (mmol/mol)	
Date of the most recent HbA1c measurement? (MM-DD-YYYY)	
Can you find another HbA1c measurement? (Y/N)	
Second most recent HbA1c reading (mmol/mol, otherwise specify unit)	
Date of the second most recent HbA1c reading? (MM-DD-YYYY)	
Can you find one or more total cholesterol measurements? (Y/N)	
Most recent total cholesterol reading (mmol/L)	
Date of the most recent cholesterol reading (MM-DD-YYYY)	
Can you find another cholesterol measurement? (Y/N)	
Second most recent cholesterol reading (mmol/L)	
Date of the second most recent cholesterol reading (MM-DD-YYYY)	
Was the patient prescribed a statin? (Y/N)	
What was the date of the statin prescription? (MM-DD-YYYY)	
What was the drug and dose?	
Does the patient have existing cardiovascular disease (CVD)? (Y/N)	
State the type of CVD	
Has the patient been prescribed acetylsalicylic acid (ASA or aspirin)? (Y/N)	

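### The hypertension-control indicator counts patients diagnosed within the 12-month window, so better case-finding in the trained arm can lower its measured control

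*Protocol article*

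**What the plan says.** The section on quantitative indicators presents Table 1 as the set of definitions the calculations will apply, so this row is fixed in the article and not left for later.

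- **Hypertension control.** The numerator is "Patients with confirmed hypertension whose last two blood pressure readings were <140/90 mm Hg". The denominator is simply "patients with confirmed hypertension". Neither sets a minimum time since diagnosis, and neither requires the two readings to come after it.
- **Sampling window.** The section on sampling patient records requires a visit in the past 12 months. That condition applies to the visit, not to the diagnosis or the readings.
- **Data available.** The Table 2 form records the date of hypertension diagnosis and the dates of the two most recent blood pressure readings. No Table 1 indicator uses the diagnosis date. For diabetes the form records the type but no diagnosis date.
- **Expected route of benefit.** The introduction says the package addresses "shortcomings among health workers in the identification and management of individuals with increased cardiovascular risk".
- **Analysis.** Change from baseline is compared between arms, with logistic models adjusted for age and gender.

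**The concern.** At follow-up, having a hypertension diagnosis is partly a post-randomisation event, and only one arm has been trained in the pathway that may produce it. The row therefore mixes two things: how well known patients are controlled, and how many patients have only recently been found.

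A clinic that finds more cases late in the window adds patients who may not yet have two post-diagnosis readings. If a raised diagnostic reading is one of the last two, the patient cannot meet the numerator.

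The planned adjustment does not deal with this. Age and gender do not carry time since diagnosis. Subtracting baseline does not cancel an inflow that arises after randomisation in one arm.

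What is at stake is the comparison under the second secondary objective. The article names blood pressure control as its example of an outcome indicator and intends the findings to inform national scale-up. A real gain in control could look smaller than it is, or absent, because detection also improved.

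**Working it through.** The article states no control rate, detection rate or target effect for this row, so there is no figure to reproduce. Every rate below is an assumption unless marked otherwise.

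**1. Who is affected.** A patient diagnosed in the window with two or more later readings is judged on post-diagnosis readings and is unaffected. With one later reading, or none, at least one of the last two dates from the diagnosis or before. If that reading is 140/90 mm Hg or above, the patient fails the numerator by construction.

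**2. Effect of extra cases.** From the article: an average of 100 sampled records per clinic. Assumed: 30 known hypertensive patients per clinic, 40% controlled; k extra new cases, 10% controlled; no change in care of known patients.

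Measured control = (30 × 0.40 + 0.10k) / (30 + k)

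- k = 3: 12.3 / 33 = 37.3%
- k = 6: 12.6 / 36 = 35.0%
- k = 10: 13.0 / 40 = 32.5%

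For the row still to show 40%, control among known patients would have to be 0.40 + 0.30k/30, which is 43%, 46% or 50%.

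**3. A second parameterisation.** Let s be the newly diagnosed share of the denominator and f the share of those with an above-target diagnostic reading among the last two. Let p_est be control in established cases and p_new control in the remaining new cases.

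Measured control = p_est(1 − s) + s(1 − f)p_new

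If p_est = p_new = p, the loss is p × s × f. At p = 30% it runs from 0.30 × 0.05 × 0.25 = 0.4 points to 0.30 × 0.30 × 1 = 9 points.

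Now let true control rise from 30% to 35%, with s = 5% at baseline. The measured change is 0.35(1 − s₁f) − 0.30(1 − 0.05f), where s₁ is the follow-up share:

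| s₁ | f = 0.25 | f = 0.75 | f = 1 |
|---|---|---|---|
| 20% | +3.6 | +0.9 | −0.5 |
| 30% | +2.75 | −1.75 | −4.0 |

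The true change is +5 points in every cell.

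**4. Is the direction certain?** Measured control falls below p_est only if (1 − f)p_new < p_est, that is, f > 1 − p_est/p_new. If established cases are at 30% and the remaining new cases at 40%, this needs f > 1 − 30/40 = 0.25. At 30% against 50% it needs f > 0.40. Below those values the inflow raises the row.

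**5. Against sampling error.** With 10 × 30 = 300 hypertensive patients per arm at 40%, the standard error of the arm difference, ignoring clustering, is √(2 × 0.4 × 0.6 / 300) = 4.0 points, so ±7.8 at 95%. The shifts in step 2 are 2.7, 5.0 and 7.5 points, all inside that margin.

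**The case against.** The strongest reply is that the link from training to more hypertension diagnoses is inferred. The article speaks of identifying people at raised cardiovascular risk through total risk assessment; it does not state that hypertension diagnoses are expected to rise. The survey figure that "76.2% of these patients are not on blood pressure-lowering medication" concerns treatment, does not separate undiagnosed from diagnosed but untreated people, and describes the population, not clinic attenders. This stands: the inflow is plausible but unquantified.

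Second, other blood pressure rows do not depend on a hypertension diagnosis: the prevalence row over all sampled adults, the low-risk row, and the very-high-risk part of the high-risk row. They would help a careful reader. None of them measures control among hypertensive patients, so they do not replace this row.

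Third, this is a pilot with a pragmatic sample size, and the illustrated shifts lie within sampling error. That limits what can be concluded from the row, but the shift is systematic and would not shrink with more records.

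A reader might also infer that the diabetes rows behave in the same way. The documents do not support that. Patients in the diabetes branch of the high-risk blood pressure row are not selected on a raised blood pressure. For the glycaemic row ("Patients with type 2 diabetes whose last two HbA1c measurements were below personal target as defined by MDA-adapted WHO PEN protocol 1"), the article does not say that HbA1c establishes the diagnosis, and the personal targets sit in an adapted protocol that is not shown. A new patient with only one HbA1c value cannot meet that numerator, but that is a missing-value matter. The glycaemic row is a possible parallel and no more.

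**Conclusion.** The point holds for the hypertension-control row. Its denominator admits patients diagnosed within the window, their last two readings may include a diagnostic one, and nothing in the stated analysis separates them. If detection rises more in the trained arm, the comparison is likely to be biased against that arm.

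The size is unknown. Under the assumed inputs, measured control falls from 40% to between 37.3% and 32.5%. Under the second set, the loss is 0.4 to 9 points. These rest on assumed control rates, an assumed inflow, and new cases being measured as less well controlled than known ones.

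It would go too far to say that every newly diagnosed patient counts as a failure, that the row must fall when detection improves, or that the pilot will be read as harmful. Patients with two later readings escape the problem, the direction can reverse, and the row need not be read alone. The issue bears on interpreting change in performance under the second secondary objective. The primary feasibility objectives are untouched.

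**What to change.** In Table 1, for the between-arm and before–after comparisons, restrict the main hypertension-control denominator to patients whose recorded diagnosis date precedes the 12-month window. At follow-up the window is the 12 months of implementation; at baseline it is the 12 months before extraction. Apply the rule identically in both arms and at both time points. The date is already on the form, so no new field is needed.

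Report patients diagnosed within the window separately as a detection measure, for example per 100 sampled adults. Report how many diagnoses are undated, and give the control result both including and excluding them.

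The cost is a smaller denominator and reliance on finding dates in unstructured paper records. Undated new cases kept in the denominator would leave some of the bias in place, which is why both versions are needed.

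No change is needed to the diabetes branch of the high-risk blood pressure row. If the sponsor wants the same split for the glycaemic row, a date of diabetes diagnosis would have to be added to the form.

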Are risk scores calculated correctly?	Proportion of patients aged 40 years or older who have visited in the last 12 months who have all measurements required for calculation of risk score within 12 months of the most recent date of visit, which have a documented risk score that is correct.	Patients aged 40 or older who have visited in the last 12 months who have all measurements required for calculation of risk score within 12 months of the most recent date of visit, which have a documented risk score that is correct.	Patients aged 40 or older who have visited in the last 12 months who have all measurements required for calculation of risk score within 12 months of the most recent date of visit, which have a documented risk score.
Are patients being risk scored?	Proportion of eligible patients with a documented risk score.	Patients aged 40 years or older who have visited in the last 12 months with a documented risk score.	Patients aged 40 years or older who have visited in the last 12 months.
Are risk scores calculated correctly?	Proportion of eligible patients with a documented risk score that is correct.	Patients aged 40 years or older who have visited in the last 12 months with a documented risk score that is correct.	Patients aged 40 years or older who have visited in the last 12 months with a documented risk score.
Are statins prescribed to the correct patients?	Proportion of eligible patients prescribed a statin.	Patients with existing CVD, patients with diabetes aged 40 years or older with high LDL values (as defined based on total CVD risk of SCORE 10%–14% in LDL≥2.6 mmol/L; with very high risk SCORE≥15% in LDL≥1.8 mmol/L), or patients with a SCORE of ≤9% and LDL≥2.6 or total cholesterol≥7.2, or patients with a SCORE of 10%–14% and LDL≥1.8 or total cholesterol≥7.2 mmol/L, or patients with a SCORE of ≥15%, prescribed a statin.	Patients with existing CVD, patients with diabetes aged 40 years or older with high LDL values (as defined based on total CVD risk of SCORE 10%–14% in LDL≥2.6 mmol/L; with very high risk SCORE≥15% in LDL≥1.8 mmol/L), or patients with a SCORE of ≤9% and LDL≥2.6 or total cholesterol≥7.2, or patients with a SCORE of 10%–14% and a LDL≥1.8 or total cholesterol≥7.2 mmol/L, or patients with a SCORE of ≥15%.

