What is the prevalence of high blood pressure?	Proportion of people whose last two systolic blood pressure reading are 140 mm Hg or above.	Patients whose last two systolic blood pressure readings were ≥140 mm Hg.	All patients aged over 18 years.

CVD, cardiovascular disease; DM, diabetes mellitus; HbA1c, glycated haemoglobin; LDL, low-density lipoprotein; SCORE, Systematic COronary Risk Evaluation.

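### Table 1 counts patients without two recorded readings as not high, or as not controlled, so better recording alone can shift these indicators between arms

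*Protocol article*

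**What the plan says.** The section on quantitative indicators in the protocol article states that the numerators and denominators printed in Table 1 are the ones to be calculated. Four places share one structure: a broad denominator, and a numerator that needs two recorded values.

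- **Prevalence of high blood pressure.** Numerator: "Patients whose last two systolic blood pressure readings were ≥140 mm Hg". Denominator: "All patients aged over 18 years".
- **Blood pressure control in hypertension.** Numerator: "Patients with confirmed hypertension whose last two blood pressure readings were <140/90 mm Hg". Denominator: everyone with confirmed hypertension.
- **Glycaemic control.** Numerator: "Patients with type 2 diabetes whose last two HbA1c measurements were below personal target as defined by MDA-adapted WHO PEN protocol 1". Denominator: everyone with type 2 diabetes.
- **Blood pressure control in high-risk patients, diabetes part.** Patients over 40 with diabetes enter the denominator whether or not two readings exist. The numerator needs two readings below the stated limit.

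The data analysis section compares the change in each indicator between intervention and control clinics, with adjustment for age and gender only. The Table 2 form asks whether a second blood pressure reading and another HbA1c value can be found, and collects their dates.

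**The concern.** Under the printed definitions, a record with no second reading is classified as a favourable result in the prevalence row and an unfavourable one in the control rows. Each indicator then mixes two things: how often patients are measured and recorded, and what the values are.

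The mixing matters because recording is unlikely to stay equal between arms. The intervention is built on total cardiovascular risk assessment, and the same table treats measurement of risk factors as a process indicator in its own right. The source records are unstructured paper, so gaps are plausible. If recording rises in trained clinics only, apparent prevalence and apparent control both rise there. Subtracting baseline does not remove this, and neither does adjustment for age and gender.

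At stake is the secondary objective of estimating change against usual-care clinics, which feeds the discussion of national scale-up. A rise in control could be read as a clinical gain, and a rise in prevalence as a worsening, when both are documentation.

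**Working it through.** The plan gives no effect size, alpha, power or recording rate for these rows, so there is no figure of its own to reproduce. The check is algebra on the printed definitions.

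**Inputs**
- T, the true share meeting the criterion, identical in both arms. The introduction gives 39.8% of adults with raised blood pressure, of whom 76.2% are untreated: 0.398 × 0.762 = 0.303. This is an assumption. The survey definition also includes diastolic pressure, so it is not the row's definition.
- r, the share of patients with two recorded readings. It is not in the document and is shown as a range. Recording is taken as unrelated to the value.

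**Formula.** Printed indicator = T × r. False gap between arms = T × (r in intervention − r in control). If r is equal at baseline, the same expression is the false difference in change.

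**Prevalence row, T = 30.3%**

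| r control v intervention | Indicator | False gap (points) |
|---|---|---|
| equal | equal | 0 |
| 80% v 90% | 24.24% v 27.27% | 3.0 |
| 50% v 60% | 15.15% v 18.18% | 3.0 |
| 50% v 70% | 15.15% v 21.21% | 6.1 |
| 50% v 80% | 15.15% v 24.24% | 9.1 |

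For 50% v 80%, the gap is 0.20 × 0.30 = 6.0 points at T = 20% and 0.398 × 0.30 = 11.9 points at T = 39.8%.

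**Hypertension control.** With assumed true control of 40%, 50% v 80% gives 20% v 32%, a false gain of 12 points. True control of 20% or 60% gives 6 or 18 points. At 40% true control, 80% v 90% gives 32% v 36%, or 4 points.

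**Chance of a significant result.** In a simulation with identical health, clinic proportions were compared by a two-sided 5% t-test: 10 v 10 clinics, 100 records each, 10,000 runs, and assumed between-clinic SDs of 0.05 for T and 0.10 for r. At T = 30.3% the prevalence row was significant in 5% of runs with equal capture, 21% for 50% v 60%, 60% for 50% v 70% and 89% for 50% v 80%. This is a simple follow-up comparison, not the planned regression.

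**Bounds.** If the unmeasured are all not high, the indicator is T × r. If all are high, it is T × r + (1 − r).
- 50% v 80%: the arm difference is 24.24 − 15.15 = +9.1 points at one bound and 44.24 − 65.15 = −20.9 at the other.
- 80% v 90%: it is +3.0 at one bound and 37.27 − 44.24 = −7.0 at the other.

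The sign reverses both times, so neither gap would be taken as a health difference.

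**Measured-only denominator.** The indicator becomes T in both arms, and the simulated rejection rate stays at 4.5% to 5.2%. This holds only because recording was assumed unrelated to the value.

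**The case against.** **The size is unknown.** Sampled patients have all visited within 12 months, and the prevalence row sets no date limit on the two readings. Capture could be high and similar in both arms, and the false gap then small. This stands, and is why a range is shown.

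**Counting the unmeasured as uncontrolled is a familiar quality convention.** That can defend a process measure. The article, however, gives blood pressure control as an example of an outcome indicator, and the convention cannot defend the prevalence row, where fuller recording makes patients look sicker.

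**An analysis plan not shown might add a missing-reading rule.** It might, but the article says the printed definitions are the ones to be calculated.

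**This is an unpowered feasibility pilot.** True. The primary objectives are not harmed, and the planned qualitative work may help explain a shift, though it does not correct one.

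**A stronger reading is tempting:** that every row limited to scored or measured patients is also defective. The documents do not support that.
- Correctness of a score, with denominator "Patients aged 40 years or older who have visited in the last 12 months with a documented risk score", has no meaning without a score. The row with numerator "Patients with a documented risk score as very high risk SCORE≥15% prescribed a statin" asks expressly about prescribing on a documented score. Both are conditional by design.
- Scoring among the fully measured already has an unconditional partner among all visitors aged 40 or older.
- Such rows shift only if newly scored patients differ from those already scored. If scoring rises from 20% to 70%, with statin use of 60% in the already scored and 20% in the newly scored, the row falls from 60% to (0.2 × 0.6 + 0.5 × 0.2)/0.7 = 31%. With equal statin use it does not move.
- Nothing says that trained clinics should measure cholesterol in everyone. The risk-measurement rows cover patients aged 40 or older.

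**Conclusion.** The concern holds for the prevalence row, the hypertension-control and HbA1c-control rows, and the diabetes part of the high-risk blood pressure row. As printed, they count patients without two readings as not high or not controlled, and nothing else in the article corrects this. Better recording in the trained arm alone would raise apparent prevalence and apparent control together.

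At an assumed true share of 30.3%, the false prevalence gap is 3.0 points for a 10-point recording difference and 9.1 points for a 30-point difference. It is zero if recording is equal. These figures rest on assumed recording rates and on recording being unrelated to the value.

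For rows restricted to patients with a documented or true risk score, the conclusion is a caution on interpretation, not a defect: case-mix can shift, so between-arm differences there should be read descriptively. Diagnosis-based denominators come from the same paper records and may also move with detection.

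**What to change.** Using data already on the Table 2 form:

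1. Add the share of patients with two blood pressure readings, and of patients with type 2 diabetes with two HbA1c values, as separate indicators by arm and wave.
2. For the prevalence and control rows, report three categories on the full denominator: not measured twice; measured and high (or not at target); measured and not high (or at target). Show the result over all patients and over those measured twice, marking the latter as descriptive because it is itself conditional on recording. Give bounds with the unmeasured all meeting, then all not meeting, the criterion.
3. Label the prevalence row as recorded prevalence. Do not interpret an arm difference in any of these rows as a change in health unless it holds across the bounds.
4. Add a note that rows limited to patients with a documented or true risk score are descriptive between arms, and that diagnosis-based denominators may move with detection.

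The cost is analysis wording and slightly more reporting, with no new data. The downside is that fewer rows will support between-arm inference, and the bounds will be wide where capture is low: at 50% capture they span 50 points.
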